## Abstract

**Background:**

There is a demand to make first-line treatments, including cognitive behavioural therapy (CBT) for adolescent anxiety disorders, more widely available. Internet-based CBT is proposed to circumvent access and availability barriers and reduce health care system costs. Recent reviews suggest more evidence is needed to establish the treatment effects of Internet-based CBT in children and adolescents and to determine related economic impacts.

**Objective:**

This pilot trial aims to collect the necessary data to inform the planning of a full-scale RCT to test the effectiveness of the Internet-based CBT program Breathe (Being Real, Easing Anxiety: Tools Helping Electronically).

**Methods:**

We are conducting a 27-month, 2-arm parallel-group, pilot randomized controlled trial (RCT). Outcomes will inform the planning of a full-scale RCT aimed to test the effectiveness of Internet-based CBT with a population of adolescents with moderate to mild anxiety problems. In the pilot RCT we will: (1) define a minimal clinically important difference (MCID) for the primary outcome measure (total anxiety score using the Multidimensional Anxiety Scale for Children); (2) determine a sample size for the full-scale RCT; (3) estimate recruitment and retention rates; (4) measure intervention acceptability to inform critical intervention changes; (5) determine the use of co-interventions; and (6) conduct a cost-consequence analysis to inform a cost-effectiveness analysis in the full-scale RCT. Adolescents aged 13-17 years seeking care for an anxiety complaint from a participating emergency department, mobile or school-based crisis team, or primary care clinic are being screened for interest and eligibility. Enrolled adolescents are being randomly allocated to either 8 weeks of Internet-based CBT with limited telephone and e-mail support, or a control group with access to a static webpage listing anxiety resources. Adolescents are randomly assigned using a computer generated allocation sequence. Data are being collected at baseline, treatment completion, and at a 3-month follow-up.

**Results:**

Currently, adolescents are being enrolled in the study. Enrolment is taking place between March 2014 and February 2016; data collection will conclude May 2016. We expect that analysis and results will be available by August 2016.

**Conclusions:**

In many communities, the resources available for front-line anxiety treatment are outweighed by the need for care. This pilot RCT is an essential step to designing a robust RCT to evaluate the effectiveness of an Internet-based CBT program for adolescents with moderate to mild anxiety problems.

**Trial Registration:**

Clinicaltrials.gov NCT02059226; http://clinicaltrials.gov/ct2/show/NCT02059226 (Archived by WebCite at http://www.webcitation.org/6epF8v7k4)

## Introduction

Anxiety disorders are the most common mental disorders diagnosed in adolescence, with prevalence before age 18 reported as greater than 30% [1,2]. The median age of onset is 11 years, making these disorders some of the earliest to develop [3]. Early onset disorders often follow a chronic course [4] and can significantly interfere with interpersonal relationships, academic performance and daily functioning [5-7]. Anxiety disorders range in severity and specific symptomology, but the more frequently diagnosed disorders in adolescents include social anxiety disorder (social phobia) [8-10], generalized anxiety disorder [8,11,12], and specific phobia [8,12]. The most prevalent is social anxiety disorder, with studies showing a two-fold increase in the prevalence of this disorder during teenage years [13,14]. The high prevalence of social anxiety disorder in adolescence can be understood in the context of developmental and environmental transitions (eg, puberty, dating, new schools, peer experiences) [9]. Undetected or undertreated, these disorders present significant future risk for adult anxiety disorders, educational underachievement, suicidality, depression, substance abuse and future hospitalization [5-7,15-19].

Cognitive behavioral therapy (CBT) as a first-line treatment for anxiety disorders in children and adolescents is well established [20,21,22] and supported by meta-analytic work [23,24,25]. CBT combines systematic exposure to feared situations with skills training and the learning of activities to help replace anxious thoughts about feared situations with more adaptive thoughts [20,21]. These treatment elements are based on the premise that repeated exposure to feared situations results in desensitization, reducing anxiety and avoidant behaviors, and improving functioning. Relaxation strategies, such as imagery and deep breathing, are included in skills training to provide ways to manage discomfort during repeated exposures [21].

Trained mental health professionals have traditionally delivered CBT, but the structured and sequential nature of CBT translates well to computer-based delivery. Within this approach, the use of the Internet as a delivery mode provides researchers with unobtrusive ways to capture data and examine access patterns, compliance, and usability issues [26]. Internet-based delivery also circumvents multiple barriers to receiving in-person CBT including: social stigma, direct and incidental costs (eg, time out of school), lack of trained deliverers, and inconvenient service times and locations [27]. This delivery method may also increase the number of young people seeking professional help. A published paper in 2002 reported that over a one-year timeframe, only 8.3% of young people with recent onset anxiety and 21.4% with chronic anxiety had sought professional help [28]. While Internet-based CBT is considered lower-intensity than in-person treatment, the majority of adolescents with anxiety disorders experience mild to moderate distress and impairment, making treatment availability paramount. Thus, Internet-based CBT is proposed to reduce demand for therapy delivered in-person, introduce cost savings, and increase timely access to recommended treatment [29].

Three recent systematic reviews of the literature have shown that self-led, computer-based and computer-assisted CBT, in combination with in-person or therapist-guided care, are viable and effective treatment approaches for children and adolescents [30,31,32]. Studies of treating adolescents using Internet-based CBT are limited to two [33,34], but provide important evidence and methodological considerations for other treatment studies. In a study targeting social fears (mainly centered on public speaking) in high school students who met the diagnostic criteria for social anxiety disorders, Tillfors et al. found that significant reductions in anxiety symptoms and improvements to mood were achieved post-intervention and maintained at one-year follow-up [34]. These treatment effects were noted as comparable to those achieved through traditional face-to-face CBT. Focusing on the treatment of adolescents who had a “markedly disturbing/disabling” anxiety disorder (predominantly generalized anxiety disorder and social phobia), Spence et al. also found that Internet-based CBT with minimal therapist support was equally efficacious as face-to-face CBT delivery in reducing anxiety symptoms post-intervention and up to one-year post-treatment [33]. The parents of participating adolescents also took part in this online program. In both studies, methods to improve treatment compliance, and the impact of compliance on treatment outcome, were noted as issues that required further investigation. Tillfors et al. reported that, of nine online modules available to complete within a 9-week period, the average number of completed modules was 2.9 [34]. Spence et al. noted that on average, adolescents and parents completed 7.5/10 and 4.48/5 sessions, respectively [33].

While the reported treatment effects of Internet-based CBT for treating adolescent anxiety are promising [33,34], published systematic reviews highlight important methodological issues that future studies must consider, in order to mature the evidence base [30,31,32]. Two reviews reported that the overall quality of the outcomes reported by studies of computerized CBT, including Internet-based CBT for adolescents, was *low* to *very low* [30,32]. Key limitations of the evidence base that were identified included: small sample sizes, intervention and comparator (waitlist or active control) differences between studies, and inconclusive treatment effects when anxiety was self-rated (versus clinician rated) [30,31,32]. Many of these limitations were also noted in the Tillfors and Spence studies [33,34]. Reviews to date have recommended that higher quality evidence is needed to firmly establish the treatment effects of computerized CBT, and that the study of associated economic impacts is needed [30,31,32].

We designed a pilot randomized controlled trial (RCT) that addresses several of the limitations highlighted in the literature to date. This pilot trial aims to collect the necessary data to inform the planning of a full-scale RCT to test the effectiveness of the Internet-based CBT program *Breathe* (Being Real, Easing Anxiety: Tools Helping Electronically). In the pilot RCT we will (1) define a minimal clinically important difference (MCID), as defined by adolescents, for the primary outcome measure, (2) determine a sample size for a full-scale RCT, (3) estimate recruitment and retention rates to determine the number of study sites needed, (4) measure intervention acceptability to inform critical intervention changes, (5) determine the use of co-interventions, and (6) conduct a cost-consequence analysis to inform a cost-effectiveness analysis for a full-scale RCT.

## Methods

### Study Design

We are conducting a 27-month, 2-arm parallel-group, pilot RCT. Eighty adolescents will be randomly assigned to either 8 weeks of Internet-based CBT with telephone and e-mail support (the *Breathe* program), or a control (minimal intervention) group with 8 weeks of access to a static webpage with general anxiety resources and information. Study enrolment is taking place from March 2014 to February 2016; data collection will conclude May 2016. Details of the study design are illustrated in Figure 1. The study has been approved by host institutions’ Research Ethics Boards.

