### Measures

#### Primary Outcome Measure

Change in anxiety symptoms in adolescents will be measured using the total score from the Multidimensional Anxiety Scale for Children (MASC2; 50 items). The MASC2 is one of the most widely used self-report measures in clinical trials in adolescents with anxiety disorders. It assesses physical symptoms, social anxiety, harm avoidance, separation/panic, and total anxiety, and has excellent 3-month test-retest reliability [40] and excellent validity [41,42]. Adolescent self-report is desirable because of the internalizing nature of anxiety [43]. The MASC2 is administered online via Intelligent Research Intervention Software (IRIS) to adolescents in the treatment group at three data collection time points: baseline (pre-treatment), 8 weeks/end of 8^th^
*Breathe* module (post-treatment) and 3 months post-treatment (follow-up). Adolescents in the control group complete the MASC2 at baseline and 8 weeks after study enrolment via IRIS. Table 1 outlines screening and outcome measurement time points.

**Table 1 table1:** Outcome measurement schedule.

	Study time points					
	Study eligibility screening	Baseline	8 weeks (postintervention)	20 weeks (3-month follow-up)	End of study enrolment period (22 months from trial start)	End of data collection period (27 months from trial start)
Demography	X					
SCARED	X					
ASQ	X					
Co-intervention use/costs			X			
MASC2		X	X	X		
MCID			X			
Treatment satisfaction			X			
Treatment adherence			X			
Number of adolescents screened					X	
Number of adolescents enrolled					X	
Number of adolescents retained at 3-month follow-up						X

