### Statistical Analyses

Adolescent reports of anxiety, intervention acceptability and adherence, use of co-interventions, recruitment and retention rates, and demography will be described by numerical summaries (mean, frequency, range, and standard deviation [SD]). The mean difference in primary outcome change scores (and SDs) from baseline to the completion of module 8 (post-intervention) will be calculated with 95% CIs. SD values from the primary outcome change scores will be used to guide the full-scale RCT sample size calculations [51]. Adolescent global ratings of change (within the ranges of +2 to +3 or -2 to -3 for reported change using the 10-point Likert scale) will serve as the estimate for the MCID value [52]. The study recruitment rate (number of adolescents enrolled during the study recruitment period) and the retention rate (number of adolescents retained at the 3-month follow-up as indicated by MASC2 completion) will be calculated. These rates will be used to determine the number of study sites and time period needed for a full-scale RCT. Frequencies and proportions (with 95% CIs) will be used to describe categorical variables (eg, gender). We will summarize characteristics of completers (>75% of modules) and non-completers, and conduct tests of association to identify particular adolescents (eg, by gender) that may benefit from additional measures to maintain engagement, and will explore potential confounders (eg, age, sex, co-morbidity) that may be adjusted for in the full-scale RCT. Mean costs (and SDs) will be calculated (with 95% CIs) using published recommendations [46,47]. To account for the amortization of intervention use after upfront costs, we will distribute the investment costs over a 3- to 5-year investment time duration using a 5% societal interest rate and using 3% and 0% rates in the sensitivity analysis. Costs for reported co-interventions (health care services) will be estimated using Alberta costing and using 2015-dollar values.

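### The stated dates contradict Table 1 and leave at most 17 weeks for a 20-week follow-up, so adolescents enrolled after about 12 January 2016 cannot complete the 3-month MASC2

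*Protocol article*

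**What the plan says.** Under Study Design the article gives calendar dates: "Study enrolment is taking place from March 2014 to February 2016; data collection will conclude May 2016". The Abstract and the Results section repeat them. Study Design also fixes the overall length: "We are conducting a 27-month, 2-arm parallel-group, pilot RCT".

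Table 1, under Primary Outcome Measure, counts from trial start instead. Its column headings include "End of study enrolment period (22 months from trial start") and "End of data collection period (27 months from trial start"). It places the last MASC2 at "20 weeks (3-month follow-up"), without distinguishing the arms.

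The text above Table 1 does distinguish them. The treatment arm is assessed at baseline, at 8 weeks or the end of module 8 ("post-treatment) and 3 months post-treatment (follow-up")). For controls it says: "Adolescents in the control group complete the MASC2 at baseline and 8 weeks after study enrolment via IRIS".

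Statistical Analyses defines retention as the number of adolescents with a MASC2 at the 3-month follow-up. Recruitment is defined alongside it: "The study recruitment rate (number of adolescents enrolled during the study recruitment period"). Both rates are to set the number of sites and the duration of the full-scale RCT.

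**The concern.** The article gives two timelines. The calendar dates put 3 months between enrolment close and data-collection close; Table 1 puts 5. The last assessment falls 20 weeks (about 4.6 months) after enrolment, so the difference decides whether late enrolees can be followed up at all.

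Estimating recruitment and retention is one of the pilot's six stated objectives. If the calendar dates are followed, some adolescents will lack the 3-month MASC2 because data collection has closed and not because they dropped out. The retention definition does not separate the two.

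**Working it through.** **Inputs.** Enrolment March 2014 to February 2016, data collection to May 2016, 27 months in total (Study Design). Enrolment ends at month 22, data collection at month 27, last MASC2 at 20 weeks = 140 days (Table 1). Planned enrolment 80, 40 per arm (Sample Size).

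**1. The article's own figures.** March 2014 to May 2016, counted inclusively, is 27 months. This reproduces. March 2014 to February 2016 is 24 months inclusive, not 22. This does not. Month 22 from 1 March 2014 is the end of December 2015.

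**2. Could a later start day explain it?** A start at the end of March 2014 brings month 22 to the end of January 2016, but month 27 then falls at the end of June 2016, not in May. Whatever the start day, Table 1 leaves 5 months between the two closing points. The calendar dates leave at most 4 (1 February to 31 May).

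**3. Time available under the calendar dates.**

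| Enrolled | Data collection closes | Days | Weeks |
|---|---|---|---|
| 1 Feb 2016 | 31 May 2016 | 120 | 17.1 |
| 29 Feb 2016 | 31 May 2016 | 92 | 13.1 |
| 29 Feb 2016 | 1 May 2016 | 62 | 8.9 |

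No reading of the two months reaches 20 weeks.

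**4. Feasibility of each timeline.**
- Calendar dates: 29 February 2016 + 140 days = 18 July 2016; 24 + 4.6 = 28.6 months, beyond 27.
- Table 1: 31 December 2015 + 140 days = 19 May 2016; 22 + 4.6 = 26.6 months, within 27.
- Last enrolment date that allows 20 weeks: 31 May 2016 − 140 days = 12 January 2016.

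**5. Adolescents affected, assuming uniform accrual.** The enrolment window, 1 March 2014 to 29 February 2016, is 731 days. 13 January to 29 February 2016 is 48 days. 48/731 = 6.6%.
- Treatment arm only (the text's schedule): 0.066 × 40 = 2.6.
- Both arms (Table 1 read without distinction): 0.066 × 80 = 5.3.
- If data collection closed on 1 May, the last feasible date is 13 December 2015; 78/731 = 10.7%, which is 4.3 of 40 or 8.5 of 80.

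Back-loaded accrual would raise these figures.

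**6. Effect on the retention rate, if those adolescents stay in the denominator.** Understatement = truncated share × the retention they would otherwise have had. At an assumed 50%: 0.066 × 0.50 = 3.3 percentage points, so 50% would appear as about 46.7%. With closure on 1 May: 0.107 × 0.50 = 5.3 points. For comparison, the 95% CI half-width at 50% is 1.96 × √(0.25/40) = 15 points for n = 40 and 1.96 × √(0.25/80) = 11 points for n = 80.

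**7. What is untouched.** 29 February 2016 + 56 days = 25 April 2016, before the end of data collection on either reading of May. The 8-week assessments remain feasible for every enrolee.

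**The case against.** The date conflict itself has no good answer; the objections concern its consequences, and most of them stand.

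- *Late enrolees are counted as lost by design.* A reader might infer this, but Statistical Analyses gives a count, with no denominator and no rule for adolescents not yet due. Such a rule is commonly left to the SAP or full protocol, which are not shown. The truncation is built into the dates; how it would be scored is not stated.
- *Five of 80 lose a visit.* This needs the 20-week MASC2 to apply to both arms. The text schedules controls only at baseline and 8 weeks, so on that text a missing 3-month MASC2 in controls comes from the schedule, not from the dates.
- *The effect is small.* About 3 points is well inside the pilot's own sampling error. True, but this is a systematic error in one direction, and it can be avoided at almost no cost.
- *The recruitment rate is also distorted.* 80/22 = 3.6 per month and 80/24 = 3.3 differ by 9%, but these are two forecasts of a fixed target. At analysis the enrolment period will be an observed fact, so the conflict need not affect the estimate.
- *Most objectives rest on 8-week data.* Change scores and their SD, the MCID, satisfaction, adherence and co-intervention use are all taken at post-intervention, as is the 20-per-arm target. This limits the point to the 3-month MASC2 and the retention rate.

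**Conclusion.** The point holds at moderate severity. The calendar dates contradict Table 1, and under them no adolescent enrolled in February 2016, nor any enrolled after about 12 January, can complete the 3-month MASC2 by 31 May 2016. Under uniform accrual this is 6.6% of enrolees: 2 to 3 of 40 in the treatment arm, or about 5 of 80 if Table 1 applies to both arms. If they are kept in the denominator, retention is understated by about 3 percentage points at an assumed 50%.

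These sizes rest on three assumptions that the article does not settle: uniform accrual, closure on the last day of May, and 50% retention at 3 months (the article's 50% dropout refers to post-intervention). The documents do not support a claim that the plan scores these adolescents as dropouts, that the primary outcome is harmed, or that the recruitment rate is necessarily wrong.

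**What to change.** Reconcile the dates in the Abstract, Study Design, Results and Table 1 in one of two ways:

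1. Close enrolment at month 22 (end of December 2015), as Table 1 has it. This keeps the 27-month length and the May 2016 close, and gives up two months of recruitment.
2. Keep enrolment open to February 2016 and extend data collection to 18 July 2016. The 27-month figure, Table 1 and the August 2016 results date then need revision. The cost is about 7 more weeks of online data collection.

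In either case:
- Compute 3-month retention only among adolescents who are scheduled for the 3-month MASC2 and whose 20-week date falls on or before data-collection close. State whether controls are scheduled for it, since the text and Table 1 differ. Limiting the denominator to those due, without also limiting it to those scheduled, would leave in controls who were never to have the visit.
- Compute the recruitment rate over the actual enrolment period.

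The two analysis rules cost nothing.

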**Figure 1 figure1:**
[figure not shown]
Trial flow diagram.

### Participants

Participants are adolescents from three Canadian provinces (Alberta, Ontario, and Nova Scotia) seeking care from a pediatric emergency department, mobile or school-based mental health team, or primary care setting that is participating as a study recruitment site. Study inclusion criteria are: (1) ages 13 to 17 years, (2) self-reported mild to moderate anxiety, (3) ability to read and write English, (4) regular access to a telephone and a computer system with high speed Internet service, and (5) ability to use a computer to interact with web material. Adolescents aged 13 to 14 years must also have a consenting parent.

Adolescents are screened for study inclusion criteria via a secure online recruitment process or telephone-based recruitment phone call. Demography is collected during the screening process to characterize adolescents who meet and do not meet clinical eligibility. Screening criteria (1), (3), (4), and (5) are assessed through yes/no answers. We are using the Screen for Child Anxiety Related Emotional Disorders (SCARED) [35] to screen for mild-to-moderate anxiety symptoms (eligibility criteria #2). The SCARED is a 41-item self-report screen for symptoms of panic disorder, social phobia and anxiety disorder, and general anxiety disorder in clinical and community adolescent samples, based on DSM-IV criteria [36,37,38]. Adolescents can report any experience of anxiety (ie, responds to any of the 41 items of anxiety symptoms/experiences as being “Somewhat/Sometimes True” or “Very/Often True”) to be considered eligible for study participation.

We are also screening for risk of suicide using the Ask Suicide-Screening Questions (ASQ) [39]. The ASQ is a brief 4-item instrument originally validated for use in emergency departments with high sensitivity for identifying the risk of suicide [39]. A “yes” response to questions 1 (“In the past few weeks, have you wished you were dead?”), 2 (“In the past few weeks, have you felt that you or your family would be better off if you were dead?”) or 4 (“Have you ever tried to kill yourself?”) on the ASQ involves a safety-follow up phone call from a research team member to evaluate intent/severity/immediacy of risk before deciding on adolescent eligibility. Adolescents who respond “yes” to question 3 on the ASQ (“In the past week, have you been having thoughts about killing yourself?”) are excluded from the study and receive brief telephone based support from a research team member to evaluate intent/severity/immediacy of risk and encourage the adolescent to seek further mental health care/crisis care.

